### 2.3. Inclusion Criteria

•Manifest obstructive CAD confirmed on CCTA with functionally significant coronary stenosis >50% or anatomically significant coronary stenosis >90% in one or more coronary vessels and appropriate anatomy for PCI.•Signed informed consent.

### 2.4. Exclusion Criteria

•Emergent PCI (e.g., acute coronary syndromes); therefore, CT processing does not delay urgent or emergent care.•Poor image quality, non-diagnostic or incomplete CCTA datasets.•No need for PCI despite positive CCTA (as per ICA or invasive physiology like RFR or FFR).•Left-main disease with >50% diameter stenosis of the left main requiring treatment.•Age < 18 years.•Pregnancy.•Lack of signed informed consent.

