### 2.6. Randomization and Study Arms

Randomization will be performed after completion of CCTA analysis and prior to invasive coronary angiography. Participants will be randomized (1:1) into two groups using sequentially numbered, opaque, sealed envelopes. The randomization sequence will be generated by an independent study nurse. Sequentially numbered, opaque, sealed envelopes will be prepared centrally and stored securely. After written informed consent and patient inclusion, the envelope will be opened immediately before PCI by a study nurse not involved in outcome assessment. Operator blinding is not feasible due to the nature of our study. For patients allocated to the intervention arm, anonymized CT datasets will be transferred securely to the image-analysis site in Switzerland (Nuclear Medicine Department) using the USZ Secure Transfer Platform (https://transfer.usz.ch/). There, detailed CT analysis and three-dimensional reconstructions will be performed using CE-marked post-processing software (GE Healthcare Advantage Workstation, AW, Version 4.7). CT data transfer requires approximately 10 min, and structured image analysis and procedural planning require approximately 30 min, ensuring cost- and time-effectiveness. Only elective PCI cases will be included, which undergo ambulatory CCTA and are then scheduled for elective PCI based on CCTA and clinical data, or if required additional stress test preprocedural findings; therefore, CT processing will not delay urgent or emergent care. The analysis results will be returned to the German study site prior to PCI and made available during the procedure. Treating operators will be informed of group allocation immediately before the PCI procedure to minimize allocation-related scheduling or case-selection bias. Participating operators have >5 years of experience in interventional cardiology and are board-certified with a formal focus in Interventional Cardiology of the German Cardiac Society (DGK).

**Intervention arm**: Full CCTA analysis, including 3D reconstructions, is displayed on an integrated monitor (3D Tabcard, CPQ-1511578) in the catheterization laboratory during PCI and can directly guide procedural decisions.

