### 2.11. Statistical Analysis

Descriptive statistics will be used to characterize the patient population, procedural details, and outcomes. Categorical variables will be reported as counts and percentages and compared using the chi-square or Fisher’s exact test. Continuous variables will be assessed for normality using the Shapiro–Wilk test. Variables that are normally distributed will be presented as mean ± standard deviation and compared using *t*-tests, while non-normally distributed variables will be presented as median (interquartile range) and compared using Mann–Whitney U tests. To assess the impact of CT planning on procedural outcomes, univariate and multivariable logistic regression models will be applied. Variables with a *p*-value < 0.10 in univariate analysis will be included in the multivariable models using a backward stepwise approach. Odds ratios (OR) with 95% confidence intervals (CI) will be reported. The primary analysis will be performed according to the intention-to-treat principle.

Procedural metrics (e.g., contrast volume, fluoroscopy time, radiation dose, procedure duration) will additionally be assessed using linear regression models. Receiver operating characteristic (ROC) curve analyses will be performed to evaluate the diagnostic performance of specific CT features (e.g., ostial angle, lesion length, plaque morphology) for predicting procedural complications or strategy changes. The area under the curve (AUC) with 95% CI will be calculated. Interobserver and intraobserver variability for CCTA-derived measurements (e.g., ostial height, takeoff angle, lesion length) will be assessed using intraclass correlation coefficients (ICC) for continuous variables and Cohen’s κ for categorical variables.

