The planned sample size of *n* = 200 patients (100 per arm) who will ultimately undergo PCI is based on prior published data on CT-guided PCI and institutional experience [3]. Since the components of the primary composite procedural optimization score have not previously been combined in a randomized trial, exact event rates are unknown. For sample size calculation, we assumed an event rate of approximately **5****0%** and a **20% absolute reduction** in the CCTA-guided arm, based on extrapolation from observational CT-guided PCI studies and institutional experience. While these assumptions may not be completely fulfilled in our real-world study setting, they provide a reasonable framework to ensure >80% statistical power to detect differences in the primary composite endpoint with a two-sided α level of 0.05 and type II error (β) of 0.20. Randomization will be performed using sequentially numbered, opaque, sealed envelopes opened immediately before PCI. Strict handling procedures are in place, and all envelope use is logged to maintain allocation concealment and integrity. Exploratory post hoc analyses will assess whether the effect of CCTA-guided planning differs according to age, sex, lesion complexity, calcification severity, bifurcation involvement, and ostial lesion location. Missing data will be handled using multiple imputation if >5% of values are missing for key variables; otherwise, complete case analysis will be performed. All statistical tests will be two-sided, with *p*-values < 0.05 considered statistically significant. Analyses will be performed using R (v4.3.1) and SPSS (v29).

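### Randomisation is placed before angiography, but patients found at angiography not to need PCI are excluded; this conflicts with the intention-to-treat claim, and the protocol's own timing statements disagree

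*Protocol article*

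**What the plan says.** Four statements in the protocol article bear on who is randomised and who is analysed.

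- Section 2.4 lists as an exclusion: "No need for PCI despite positive CCTA (as per ICA or invasive physiology like RFR or FFR".
- Section 2.6 fixes the order: "Randomization will be performed after completion of CCTA analysis and prior to invasive coronary angiography".
- Section 2.11 sizes the trial at 200 "patients (100 per arm) who will ultimately undergo PCI".
- Section 2.11 also states: "The primary analysis will be performed according to the intention-to-treat principle".

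Section 2.6 contains two further timing statements: "the envelope will be opened immediately before PCI by a study nurse not involved in outcome assessment", and "Treating operators will be informed of group allocation immediately before the PCI procedure". Section 2.11 repeats that envelopes are opened just before PCI. For patients allocated to the intervention arm, Section 2.6 gives the work that follows allocation: "CT data transfer requires approximately 10 min, and structured image analysis and procedural planning require approximately 30 min".

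The article does not say how a randomised patient who has no PCI is scored or counted.

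**The concern.** The exclusion depends on the result of angiography or a pressure-wire measurement. If allocation precedes angiography, as Section 2.6 says, it removes patients after randomisation. The 200 are then a subset defined by what happened after allocation, which an intention-to-treat analysis is meant to avoid.

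Loss of numbers is the smaller problem. Section 2.6 says operators cannot be blinded and that the CT analysis may guide decisions in the catheterisation laboratory. Section 2.8 collects operators' views on whether CT planning helped avoid unnecessary PCI, so the protocol itself regards an influence on the PCI decision as conceivable. If such an influence led to different kinds or numbers of patients being excluded in the two arms, the PCI-only comparison would no longer be between randomised groups. If the intervention arm excluded more low-risk patients, CT guidance would look worse than it is; if it excluded fewer, better.

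**Working it through.** **1. Order of events.** Under the explicit sentence in Section 2.6 the order is CCTA analysis, randomisation, angiography and physiology, decision on PCI, PCI. The Section 2.4 criterion acts at the fourth step, after randomisation. If opening the envelope immediately before PCI means after angiography and physiology, the order is CCTA analysis, angiography and physiology, decision on PCI, allocation, PCI, and the criterion acts before allocation. Both orders can be read from Section 2.6, and they cannot both hold. The second also fits poorly with about 10 + 30 = 40 minutes of transfer and analysis that Section 2.6 describes for allocated patients, with results returned before PCI.

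**2. The plan's own power figure.** Inputs from Section 2.11: 50% against 30%, two-sided alpha 0.05, 100 per arm. Normal approximation with pooled variance under the null:

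- power = Φ{[d√n − 1.96√(2p̄(1−p̄))] / √(p1(1−p1) + p2(1−p2))}
- d = 0.20, n = 100, p̄ = 0.40: (2.000 − 1.358) / 0.678 = 0.947, so power = 82.8%.

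The stated figure of more than 80% reproduces. It applies to 200 patients who have had PCI.

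**3. Number to randomise.** The documents give no rate of no PCI after randomisation; call it q (assumption). Randomised = 200/(1 − q), rounded up:

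| q | Randomised for 200 PCI patients |
|---|---|
| 10% | 222.2, so 223 |
| 20% | 250 |
| 30% | 285.7, so 286 |

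**4. Power if everyone randomised is analysed.** Further assumption: every no-PCI patient is event-free in both arms. The event rates become 0.50(1 − q) and 0.30(1 − q).

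| q | Rates | Randomised | Power | n per arm for 80% power |
|---|---|---|---|---|
| 10% | 45% vs 27% | 223 | 80.4% | 111 |
| 20% | 40% vs 24% | 250 | 77.7% (exact chi-square 78.0%) | 133 |
| 30% | 35% vs 21% | 286 | 75.3% | 161 |

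For q = 20%: d√n = 0.16 × √125 = 1.789; 1.96√(2 × 0.32 × 0.68) = 1.293; √(0.24 + 0.1824) = 0.650; (1.789 − 1.293)/0.650 = 0.763; power = 77.7%.

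**5. Illustration of possible bias, with no true effect.** Assumptions: the event rate would be 50% in both arms if all had PCI, and excluded patients would have had rate r. The PCI-only rate is (0.50 − qr)/(1 − q). Exclude 10% in one arm and 20% in the other:

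- r = 0: 0.50/0.90 = 55.6% against 0.50/0.80 = 62.5%, a spurious 6.9 points.
- r = 20%: 0.48/0.90 = 53.3% against 0.46/0.80 = 57.5%, a spurious 4.2 points.
- Equal q and equal r in both arms: zero.

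Swapping the arms reverses the sign. None of these exclusion rates comes from the documents.

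**The case against.** The strongest reply is that the envelope is opened immediately before PCI and the operator learns the allocation then, a step Section 2.6 says is meant to limit scheduling and case-selection bias. If that means after angiography and physiology, the exclusion precedes allocation and the bias objection falls. This stands as a possible reading. It does not settle the matter, because it contradicts the explicit sentence placing randomisation before angiography and leaves little room for the 40 minutes of work.

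A second reply is that the criterion rests on angiography or invasive physiology and not on the CT package, that the item on avoided PCI is operator opinion, and that entry already requires functionally significant stenosis above 50% or anatomical stenosis above 90% with anatomy suitable for PCI. All of that is correct. A reader might infer that the exclusion is an outcome of the intervention; the documents show only that an influence is conceivable.

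A third concerns power. A reader might take 200 as the number randomised and, with 20% without PCI and event-free, arrive at about 69% (exact chi-square 68.7% for 40% against 24% at 100 per arm). Section 2.11 does not support this, since it counts 200 who undergo PCI; the matching figure at that rate is 250 randomised and about 78%. Even that treats no-PCI patients as event-free, although contrast, radiation, troponin and hospital stay can be scored without PCI.

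Finally, the article is a condensed account and its flowchart is not shown, so the enrolment figure may stand elsewhere. That excuses an absent number; it does not reconcile statements that conflict on the page.

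**Conclusion.** The point holds as a conflict in the stated rules: timing of randomisation, exclusion criterion, counted population and intention-to-treat principle cannot all be followed as written, and the two timing statements disagree. It needs correcting because the validity of the primary comparison depends on which order is used.

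A reader might go further and conclude that the analysis is definitely not intention-to-treat. The documents do not support that: the article nowhere says outright that randomised patients without PCI are dropped, and one reading of the envelope text removes the problem.

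If allocation does precede angiography, bias is possible, with size and direction unknown. The 4 to 7 points in the illustration rest wholly on assumed exclusion rates and risks; they show only that modest imbalance could matter beside an assumed 20-point effect. The effect on power is moderate: over assumed no-PCI rates of 10 to 30%, analysing all randomised patients with 200 reaching PCI gives about 80% down to 75%, if no-PCI patients are event-free.

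**What to change.** Reconcile Sections 2.4, 2.6 and 2.11 in one of two ways, before the first envelope is opened.

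(a) State that the envelope is opened only after angiography or physiology has confirmed that PCI will be done, and delete the sentence placing randomisation before angiography. The exclusion then precedes allocation, and the 200 are the randomised patients. The cost is logistical: the CT package must be ready beforehand, whichever arm the patient will enter, or the procedure must be staged.

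(b) Keep allocation before angiography and remove this criterion as a post-randomisation exclusion. Define the primary intention-to-treat set as every patient whose envelope was opened. Score all six components from the index catheterisation whether or not PCI followed. Report the no-PCI proportion by arm and keep the PCI-only set as a supportive analysis. Restate sample size and power in randomised patients, with the assumed no-PCI rate given. The cost is a change of wording and a larger target: at 20% without PCI, and those patients event-free, 2 × 133 = 266 randomised would be needed for 80% power.

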### 2.5. CCTA Acquisition and Analysis

Coronary computed tomography angiography will be performed in accordance with Society of Cardiovascular Computed Tomography (SCCT) guidelines. Prior to image acquisition, intravenous beta-blockade (metoprolol) will be administered in individually titrated doses to achieve a target heart rate below 65 beats per minute whenever feasible. Sublingual nitrates will be routinely administered for coronary vasodilation.

The acquisition protocol is individualized based on patient-specific parameters, including heart rate, heart rhythm, and body habitus. In the majority of cases, ECG-triggered prospective axial acquisition will be employed. Patients with persistently elevated heart rates (>80 bpm) despite beta-blocker administration or with frequent ectopic beats will undergo ECG-triggered prospective arrhythmia-adapted axial scanning or spiral acquisition with retrospective ECG-gated reconstruction. In patients with stable heart rates below 65 bpm and a body mass index (BMI) < 28 kg/m^2^, a prospectively ECG-triggered high-pitch spiral acquisition protocol will be performed [10].

All examinations will be performed using a third-generation dual-source CT scanner (SOMATOM Force, Siemens Healthineers, Forchheim, Germany) capable of 384-slice acquisition (2 × 192 detector rows). Scan parameters will be adapted to patient BMI and included a tube voltage range of 80–120 kVp and tube current of 290–560 mA. Images will be reconstructed using a 512 × 512 matrix, with a slice thickness of 0.8 mm and an increment of 0.4 mm. For contrast enhancement, 50–60 mL of iodinated contrast medium (iopromide, Ultravist^®^, Bayer Healthcare, Berlin, Germany) will be administered via an antecubital vein at a flow rate of 5 mL/s, followed by a 50 mL saline flush at the same injection rate. Image acquisition will be timed to the arterial contrast phase using ECG gating.

CCTA scans will be analyzed by experienced readers with >5 years of CCTA experience, level 2/3 certified by the German Society of Cardiology. CAD-RADS 2.0 will be used to categorize the degree of lumen narrowing as follows: (0) none (0%), (1) minimal (1–24%), (2) mild (25–49% stenosis), (3) moderate (50–69% stenosis), (4) severe (70–99% stenosis), or (5) chronic total occlusions (100%) [11].

### 2.6. Randomization and Study Arms

Randomization will be performed after completion of CCTA analysis and prior to invasive coronary angiography. Participants will be randomized (1:1) into two groups using sequentially numbered, opaque, sealed envelopes. The randomization sequence will be generated by an independent study nurse. Sequentially numbered, opaque, sealed envelopes will be prepared centrally and stored securely. After written informed consent and patient inclusion, the envelope will be opened immediately before PCI by a study nurse not involved in outcome assessment. Operator blinding is not feasible due to the nature of our study. For patients allocated to the intervention arm, anonymized CT datasets will be transferred securely to the image-analysis site in Switzerland (Nuclear Medicine Department) using the USZ Secure Transfer Platform (https://transfer.usz.ch/). There, detailed CT analysis and three-dimensional reconstructions will be performed using CE-marked post-processing software (GE Healthcare Advantage Workstation, AW, Version 4.7). CT data transfer requires approximately 10 min, and structured image analysis and procedural planning require approximately 30 min, ensuring cost- and time-effectiveness. Only elective PCI cases will be included, which undergo ambulatory CCTA and are then scheduled for elective PCI based on CCTA and clinical data, or if required additional stress test preprocedural findings; therefore, CT processing will not delay urgent or emergent care. The analysis results will be returned to the German study site prior to PCI and made available during the procedure. Treating operators will be informed of group allocation immediately before the PCI procedure to minimize allocation-related scheduling or case-selection bias. Participating operators have >5 years of experience in interventional cardiology and are board-certified with a formal focus in Interventional Cardiology of the German Cardiac Society (DGK).

**Intervention arm**: Full CCTA analysis, including 3D reconstructions, is displayed on an integrated monitor (3D Tabcard, CPQ-1511578) in the catheterization laboratory during PCI and can directly guide procedural decisions.

**Control arm**: The operator reviews the standard clinical CCTA report and images prior to ICA/PCI according to institutional standard operating procedures, without structured quantitative post-processing, procedural planning recommendations, or real-time visualization in the catheterization laboratory.

### 2.7. PCI Procedure and CT-Guided Planning

Interventional cardiologists will receive a standardized CCTA report prior to the PCI procedure during the pilot study phase for all patients and during the randomized study for the patients randomized to the CCTA-guided PCI arm. The report contains annotated images and textual descriptions covering optimal angiographic projections, reference vessel diameters, lesion length, calcium distribution, and bifurcation anatomy to guide stent and device selection. A representative file report is provided in the Supplementary Materials, illustrating how quantitative and actionable information is communicated consistently to the operator. Procedural planning includes:•Maximal Intensity Projection (MIP) images of the coronary tree.•Exact location and height of coronary ostia.•Axial images of coronary arteries.•Multiplanar reformation (MPR) images of coronary arteries.•Short-axis cross-sectional images.•Lesion length.•Bifurcation anatomy and vessel tortuosity, as well as a suggested provisional stenting versus a two-stent approach.•Calcification burden, including the arc of the calcification in degrees and the calcification length.•Lesion morphology, including the presence and extent of mixed and non-calcified plaques.•Optimal C-arm angulation angles.•The need for lesion preparation (rotational atherectomy or intravascular lithotripsy), choice of guiding catheter, stenting strategy, and projection angles may be adapted accordingly.

Intravascular imaging will not be discouraged in either study arm and will be encouraged in both arms in certain clinical scenarios and based on current guideline recommendations. Thus, operators may perform IVI based on pre-specified bail-out criteria, including uncertain lesion length or morphology, suboptimal stent expansion or malapposition, complex bifurcation anatomy, heavy calcification, or any safety concern. All IVI use, including specific indications for imaging, will be prospectively documented. Notably, the “need for IVI” in the composite endpoint reflects procedural escalation and resource utilization and not an adverse clinical event.

### 2.8. Data Collection

Data will be collected prospectively and will be entered into a standardized database. The collected variables include:▪**Demographics**: age, gender, date of admission, and length of hospitalization.▪**Indications for CCTA and ICA**: typical angina pectoris, atypical angina pectoris, non-anginal chest pain, or presence of dyspnea.▪**Medical history and cardiovascular risk factors**: prior myocardial infarction, hypertension, dyslipidemia, diabetes mellitus, current or prior cigarette smoking, chronic obstructive pulmonary disease, chronic kidney disease, atrial fibrillation, or peripheral artery disease.▪**Cardiac medications at baseline.**▪**Echocardiographic data**: left ventricular ejection fraction (LVEF) or presence of regional wall motion abnormalities.▪**CCTA data:**oAnatomic lesion location, including segment number and classification into proximal, mid, or distal vessel.oOstial involvement and measurement of coronary ostium height from the aortic annulus.oTakeoff angle of right and left coronary ostia, assessed using clock-face reference.oPlaque composition (calcified, non-calcified or mixed based on the presence of the calcified content by visual criteria of >80%, 20–80% and <20% calcium content) [12].oPresence of high-risk plaque features, including: positive remodeling, napkin-ring sign, low attenuation plaque (<30 HU) or spotty calcification [13].oTotal coronary calcium score quantified using the Agatston score.▪**Invasive procedural data**: Comprehensive data from invasive coronary procedures will be collected, including: use of advanced intracoronary imaging (IVUS if necessary), use of physiological assessment (FFR or iFR/RFR if necessary), number of stents implanted, their total length, stent diameters, the use of re-dilation, including the use of scoring balloons and the corresponding pressures, and the use of lesion modification techniques (rotablation or/and intravascular lithotripsy), and bifurcation stenting strategies including provisional versus bifurcation stenting if necessary.▪**Procedural outcomes and metrics**: Final TIMI flow grade, residual stenosis in percentage, procedural success, defined as final TIMI 3 flow with <20% residual stenosis in the treated segment and absence of in-hospital major adverse procedural events, additional procedural metrics included total fluoroscopy time (minutes), radiation exposure (mGy), contrast volume used (ml), and total procedure duration (minutes).▪**Operator feedback and satisfaction:**oUse of CT-based projections during PCI.oPrediction of stent dimensions (length and diameter) based on CCTA measurements.oPrediction of landing zones for stent deployment.oSatisfaction with CCTA planning (1–5 scale for both primary and secondary operators).oPerceived benefit of CCTA-derived data on ostial angle, lesion length, plaque quality and projection guidance, helping with reducing procedure time, fluoroscopy exposure and complications.oWhether CCTA planning helped in avoiding unnecessary PCI or reducing the number of stents required for lesion treatment.
